## Treatment strategies

### Standard procedures in control arm (arm A)

Patients included in the study should undergo surgery within 6 weeks after signing the informed consent. Local treatment (resection and/or open ablation) of the CRLM in both arms is in accordance with the national guidelines. An intra-operative ultrasound evaluation of the liver will be performed to assure the feasibility of complete resection of the CRLM with an adequate liver remnant. Resection of CRLM can be performed either by minimal-invasive (laparoscopic or robotic) or open approach at the discretion of the surgeon.

### Investigational procedures of the experimental arm (arm B)

The treatment of patients randomized to the experimental arm consists of HAI pump placement following complete resection and/or open ablation of all CRLM. Pump implantation will be cancelled in patients with unexpected unresectable CRLM or EHD detected at the time of surgery. Implantation of the HAI pump (Tricumed IP2000V infusion pump; Fig. 2) is performed by an open or minimal-invasive approach. In patients requiring simultaneous resection of the primary tumor and CRLM, the colorectal resection is performed after pump placement to reduce the risk of pump contamination. The implantation procedure of the infusion pump and dose adjustment protocols have been discussed by previous authors and was optimized for the materials used in this trial [14, 15]. In addition to local treatment of the CRLM, a cholecystectomy is performed to avoid cholecystitis as a result of inadvertent intra-arterial chemotherapy of the gallbladder [16]. The pump catheter is positioned in the gastroduodenal artery (GDA) allowing perfusion of the entire liver without obstructing the flow in the hepatic artery. The pump catheter has rings at the distal end that allow for securing the catheter with non-absorbable ties in the GDA (Fig. 3). In patients with abnormal hepatic arterial anatomy, the GDA is still the preferred site, as long as it connects with a proper hepatic artery perfusing at least one segment of the liver. Perfusion of the entire liver can be achieved in these patients by ligating all accessory and replaced hepatic arteries. Intrahepatic shunts will typically reassure that the catheter perfuses all liver segments.

**Fig. 2 Fig2:**
[figure not shown]
Tricumed infusion pump

**Fig. 3 Fig3:**

Distal tip of the intra-arterial catheter

The entire GDA and the proximal proper hepatic artery are mobilized and dissected circumferentially from their attachments to facilitate insertion of the catheter and to avoid inadvertent perfusion of the pancreas, stomach, or duodenum. Branches to the retroperitoneum arising from the right or left hepatic artery are common and should be ligated. The use of papaverine is optional to gain additional dilatation of the GDA.

Before implantation, a function test of the pump is performed to confirm flow. The pump pocket should be created in the left lower quadrant so that contact with the anterior superior iliac spine and the lower ribs is avoided. The pocket cavity should be 3/4 caudal to the incision to ensure an optimal position of the septum for refills. The catheter is tunneled through the abdominal wall into the abdominal cavity. The pump is secured to the abdominal fascia with nonabsorbable sutures; the catheter should be positioned behind the pump to prevent catheter injury by a needle when accessing the pump percutaneously.

Next, the GDA is ligated with a nonabsorbable tie as far away (at least 2 cm) from the common hepatic artery as possible. Vascular control of the common and proper hepatic arteries is achieved with vascular clamps or vessel loops. Isolated vascular control of the GDA at its orifice can be used alternatively to avoid occlusion of the hepatic artery. A transverse arteriotomy is made in the distal GDA, and the catheter is inserted up to but not beyond the junction with the hepatic artery (Fig. 4). If the catheter protrudes into the common hepatic artery, turbulence of blood flow can lead to increased risk of thrombosis of the hepatic artery. Failure to pass the catheter to the junction leaves a short segment of the GDA exposed to full concentrations of floxuridine without the diluting effect of blood flow, potentially resulting in sclerosis, thrombosis, pseudo-aneurysm with bleeding, or late dislodgment. When positioned, the catheter should be secured with three to four nonabsorbable ties (silk 2.0) proximal to the tying rings on the catheter. Perfusion of both lobes of the liver and lack of extrahepatic perfusion is confirmed by a bolus injection of methylene blue. After the perfusion test, the catheter is flushed with heparinized saline, and the wounds are closed.

**Fig. 4 Fig4:**
[figure not shown]
Intra-arterial positioning securing of distal tip of the catheter. Arrow: Tip of the catheter is positioned at the orifice of the GDA

### Postoperative procedures experimental arm

Prior to the first administration of intra-arterial chemotherapy, bilobar hepatic perfusion and lack of extrahepatic perfusion are confirmed by:A multiphase or perfusion CT with contrast injection through the bolus port of the pump.Technetium-99-labeled macroaggregated albumin (Tc-99 m MAA) scintigraphy. Tc-99 m MAA is administered through the pump bolus port. Within 1 h after Tc-99 M MAA injection, both planar imaging and a SPECT/CT scan are performed.

Patients with extrahepatic perfusion are evaluated angiographically and aberrant branches embolized with re-testing prior to treatment.

### Drug treatment plan experimental arm

The drug that is used for HAIP is floxuridine (also known as fluorodeoxyuridine (FUDR), Fresenius Kabi, LLC, USA). HAIP chemotherapy with floxuridine has been administered since the early eighties for patients with CRLM in the adjuvant, neo-adjuvant, and induction chemotherapy setting [10, 16–24]. Floxuridine has a half-life of 10 min and the liver extracts 95% of floxuridine during the first pass [8]. Toxic effects have been well characterized. The pump reservoir is filled percutaneously with 0.12 mg/kg floxuridine together with 35,000 U of heparin, 25 mg of dexamethasone, and enough normal saline for a total volume of 35 mL. For patients who are more than 25% above ideal body weight, the actual dose of floxuridine is calculated by using a weight that averages the patient’s actual weight and their ideal weight. Patients will have HAIP administered in a 4-weeks-cycle, with a total of 6 cycles. On day 1, the pump reservoir is filled with floxuridine, dexamethasone, and heparinized saline. On day 15, the pump is emptied and refilled with heparinized saline (35,000 U of heparin and enough normal saline for a total volume of 35 mL) for 2 weeks. Until completion of HAIP chemotherapy, patients will receive a prophylactic proton-pump inhibitor once daily. The use of NSAIDs is discouraged during HAIP treatment. Patients’ complete blood counts and liver tests are monitored every 2 weeks during HAIP chemotherapy. In patients with abnormal liver values, dose reduction or discontinuation of HAIP chemotherapy is performed according to a predetermined protocol (Table 1). Dexamethasone (25 mg) is added to the heparinized saline in case of toxicity according to the values in Table 1 resulting in cessation of floxuridine.

**Table 1 Tab1:** Dose adjustment schedule

	Reference Value (RV)^a^ Upper limit of normal	% floxuridine dose
Aspartate aminotransferase	2–3 ^a^ RV	80%
	3–4 ^a^ RV	50%
	> 4 ^a^ RV	Hold
Alkaline phosphatase	1.2–1.5 ^a^ RV	50%
	> 1.5 ^a^ RV	Hold
Total bilirubin	1.2–1.5 ^a^ RV	50%
	> 1.5 ^a^ RV	Hold

^a^Reference value is defined as the patient’s value on the first day of the most recent floxuridine dose

## Follow-up

Follow-up for patients both randomized to arm A and arm B will be performed with CEA measurement and abdominal and chest CT including 4-phase liver imaging (year 1–3: every 3 months; year 4–5: every 6 months). The surgical complication score is measured 2 weeks and 3 months after surgery. The chemotherapy toxicity score is measured 2 weeks, three and 6 months after surgery. Quality of life is measured in both arms at baseline, every 3 months in the first year, and 2 and 5 years after surgery.

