**Methods:**

This is an open label multicenter RCT. A total of 230 patients with resectable CRLM without extrahepatic disease will be included. Only patients with a clinical risk score (CRS) of 0 to 2 are eligible, meaning: patients are allowed to have no more than two out of five poor prognostic factors (disease-free interval less than 12 months, node-positive colorectal cancer, more than 1 CRLM, largest CRLM more than 5 cm in diameter, serum Carcinoembryonic Antigen above 200 μg/L). Patients randomized to arm A undergo complete resection of CRLM without any adjuvant treatment, which is the standard of care in the Netherlands. Patients in arm B receive an implantable pump at the time of CRLM resection and start adjuvant HAIP chemotherapy 4–12 weeks after surgery, with 6 cycles of floxuridine scheduled. The primary endpoint is progression-free survival (PFS). Secondary endpoints include overall survival, hepatic PFS, safety, quality of life, and cost-effectiveness. Pharmacokinetics of intra-arterial administration of floxuridine will be investigated as well as predictive biomarkers for the efficacy of HAIP chemotherapy. In a side study, the accuracy of CT angiography will be compared to radionuclide scintigraphy to detect extrahepatic perfusion. We hypothesize that adjuvant HAIP chemotherapy leads to improved survival, improved quality of life, and a reduction of costs, compared to resection alone.

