## Methods/design

### Objective

The primary aim is to compare the progression-free survival (PFS) of surgery with adjuvant HAIP chemotherapy to surgery alone in patients with resectable CRLM with a low CRS 0–2 points). Secondary objectives are to compare OS, postoperative complications, adverse events, quality of life, and costs between the two arms. Pharmacokinetics of intra-arterial administration of floxuridine will be investigated as well as predictive biomarkers for the efficacy of HAIP chemotherapy. In a side study, the accuracy of CT angiography will be compared to radionuclide scintigraphy to detect extrahepatic perfusion.

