## Safety analysis

Interim analyses are performed for postoperative complications (grade 3 or higher) and adverse events (serious adverse events plus adverse events of grade 3 or higher) for early detection of unusually high rates of complications and adverse events in the experimental arm (arm B). Interim analyses are planned after inclusion of 20 and 50 patients in arm B.

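### Both scheduled safety scores end before pump use does, so the complication comparison leaves out late pump and catheter events in arm B

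*Protocol article*

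**What the plan says.** The Follow-up section of the protocol article sets two safety scores. For the first, "The surgical complication score is measured 2 weeks and 3 months after surgery". For the second, "The chemotherapy toxicity score is measured 2 weeks, three and 6 months after surgery".

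The Abstract (Methods) says that arm B patients receive the pump at resection and "start adjuvant HAIP chemotherapy 4–12 weeks after surgery, with 6 cycles of floxuridine scheduled". The section Drug treatment plan experimental arm adds: "Patients will have HAIP administered in a 4-weeks-cycle, with a total of 6 cycles". Within each cycle, "On day 15, the pump is emptied and refilled with heparinized saline", so pump and catheter stay in use during the two weeks without floxuridine.

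The surgical description in the arm B procedures (text after the Fig. 3 caption) considers a catheter tip that stops short of the junction with the hepatic artery. A short segment of the gastroduodenal artery is then exposed to undiluted floxuridine, "potentially resulting in sclerosis, thrombosis, pseudo-aneurysm with bleeding, or late dislodgment".

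The Objective section treats complications and adverse events as separate comparisons: "Secondary objectives are to compare OS, postoperative complications, adverse events, quality of life, and costs between the two arms".

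**The concern.** A 3-month window suits complications of a liver resection. It fits poorly with an implanted pump and arterial catheter that are accessed every two weeks for about half a year, starting one to three months after the operation. Most of the period in which the device is used for treatment lies after the last surgical score. The one foreseen mechanism that depends on floxuridine exposure cannot begin before week 4–12.

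Postoperative complications are a stated between-arm comparison. Arm A has no pump, so a device event after month 3 can be lost only from arm B. If that comparison rests on the scheduled score, the direction of any distortion is known: arm B looks better than it is. This matters for adoption, since the Discussion reports that an earlier 26-centre trial of intra-arterial chemotherapy was terminated early because of high complication rates.

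**Working it through.** The article gives no week in which pump use ends, so there is no stated figure to reproduce. The check is calendar arithmetic on the stated schedule, assuming no treatment delay.

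**Inputs**
- Start of treatment: week 4 to week 12 after surgery (Abstract, Methods).
- Duration: 6 cycles × 4 weeks = 24 weeks (Drug treatment plan).
- Last surgical complication score: 3 months (Follow-up).
- Last chemotherapy toxicity score: 6 months (Follow-up).
- One month = 52.18 / 12 = 4.348 weeks, so 3 months = week 13.0 and 6 months = week 26.1.

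**End of scheduled pump use** = start + 24 weeks
- Earliest start: 4 + 24 = week 28.
- Latest start: 12 + 24 = week 36.

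**Gap after the last surgical score** = end − 13.0
- Earliest start: 28 − 13.0 = 15.0 weeks.
- Latest start: 36 − 13.0 = 23.0 weeks.

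**Share of the treatment period after the last surgical score** = gap / 24
- Earliest start: 15.0 / 24 = 62%.
- Latest start: 23.0 / 24 = 96%.

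The pump is implanted at surgery, so exposure can also be counted from the operation. The share is then gap / end: 15.0 / 28 = 53% and 23.0 / 36 = 64%. More than half of the device period still follows the last score.

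**Gap after the last toxicity score** = end − 26.1
- Earliest start: 28 − 26.1 = 1.9 weeks.
- Latest start: 36 − 26.1 = 9.9 weeks.

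The last floxuridine infusion ends two weeks before cycle 6 does, at start + 5 × 4 + 2: week 26 for the earliest start and week 34 for the latest. For the earliest start the 6-month toxicity score therefore coincides with the end of floxuridine. For the latest start, about 34 − 26.1 = 7.9 weeks remain.

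**What cannot be computed.** The number of events missed would need a device complication rate over time and the window in which adverse events are collected. The article gives neither, so the shares above describe time, not events.

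**The case against.** The surgical score is not the only route by which device harm is recorded. The Objective section lists adverse events as a comparison of their own, and Secondary endpoints lists safety as a whole. Safety analysis describes interim looks at postoperative complications of grade 3 or higher and, separately, at "adverse events (serious adverse events plus adverse events of grade 3 or higher"), with no 3-month limit on either. A late dislodgment with bleeding would fit there. The adverse event window, the classification of device events and the content of the case report form are details that an article may leave to the full protocol. The list of late catheter events is conditional on a tip that fails to reach the junction, which the described technique is meant to avoid, and it carries no frequency. Arm B patients also have blood counts and liver tests every two weeks during treatment, so device problems may well be noticed.

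Most of this stands, and it limits the point. A reader might infer that device harm in arm B is undercounted in the trial as a whole. The article does not support that, because serious and grade 3 or higher events have another route. A reader might also infer that costs are biased in favour of HAIP, but nothing says that costs are derived from the surgical score. Nor is the 3-month cut-off shown to affect arm B alone in every respect: both arms have liver surgery and share the cut-off, and only events specific to the pump and catheter are confined to arm B.

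Two things survive. The timing of both scores is stated, not left out, and neither reaches the end of cycle 6. And the adverse event definition given for the interim looks does not cover non-serious events below grade 3, so lower-grade device events after month 3 have no stated place in either comparison.

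**Conclusion.** The point holds in a limited form. The article ends the surgical complication score 15–23 weeks before scheduled pump use ends, with 62–96% of the treatment period still to come, and ends the toxicity score 1.9–9.9 weeks before the end of cycle 6. A complication comparison built on the scheduled score leaves out late pump and catheter events, which only arm B can have.

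The consequence is a risk of undercount, confined to that comparison and to lower-grade device events. Undercounting of safety overall is not shown, and no percentage of missed events can be given. The conclusion assumes that the surgical score is the measure behind the postoperative complication comparison (the article schedules no other), that all six cycles are given without delay, and that 3 and 6 months mean weeks 13 and 26. Delays would widen the gaps; early discontinuation would shorten them.

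**What to change.** - Keep the 2-week and 3-month surgical complication score in both arms, so that the comparison of the operations is unchanged.
- In arm B, add an item for pump and catheter complications of any grade, completed at the existing 3-monthly follow-up until the pump is removed or permanently out of use.
- Extend the toxicity score to the end of cycle 6. The existing 9-month follow-up (9 × 4.348 = week 39.1) is the first that falls after week 36.
- State under which safety outcome pump and catheter events count. Report device complications to the end of pump use beside the 90-day surgical rate.

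The cost is one extra case report form item and a later toxicity reading, at follow-up that already takes place. It requires no additional procedure and no change to treatment. Arm B's reported complication rate will look less favourable. Because the device item is collected in arm B only, it should be reported descriptively and not tested against arm A.

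### The chemotherapy toxicity score is timed from surgery and stops at 6 months, before the sixth HAIP cycle ends and with no reading after treatment

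*Protocol article*

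**What the plan says.** The Follow-up section of the protocol article fixes three readings, all counted from surgery: "The chemotherapy toxicity score is measured 2 weeks, three and 6 months after surgery". It lists no later one.

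The treatment calendar is set elsewhere. The Methods part of the abstract has arm B patients "start adjuvant HAIP chemotherapy 4–12 weeks after surgery, with 6 cycles of floxuridine scheduled". The section on the drug treatment plan gives the cycle length: "Patients will have HAIP administered in a 4-weeks-cycle, with a total of 6 cycles". Floxuridine occupies the first half of each cycle: "On day 15, the pump is emptied and refilled with heparinized saline", which stays in for the remaining 2 weeks.

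Two other sources of safety data are described. During treatment, "complete blood counts and liver tests are monitored every 2 weeks during HAIP chemotherapy". The Safety analysis section also has interim reviews of postoperative complications of grade 3 or higher and of "adverse events (serious adverse events plus adverse events of grade 3 or higher"), planned after 20 and 50 inclusions in arm B.

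Safety is a secondary endpoint, and the Objective section names adverse events among the outcomes to be compared between arms.

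**The concern.** The score is anchored to surgery, whereas exposure to the drug is anchored to a start date that may vary by 8 weeks. A reading at a fixed time after surgery therefore captures different amounts of treatment in different patients, and the last reading falls while treatment is still planned to continue. Toxicity that builds up over cycles, or appears after the last one, has no scheduled score.

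At stake is the benefit-risk reading of the trial. If HAIP improves progression-free survival, the case for adopting it will be weighed against its toxicity. A scored summary that ends before treatment does could make arm B look more tolerable than it was. Lower-grade events not scored at the time are hard to recover later.

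**Working it through.** The plan gives no figure to reproduce on this point; the check is calendar arithmetic on its own schedule.

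**Inputs**
- Toxicity score: 2 weeks, 3 months, 6 months after surgery (Follow-up).
- HAIP start, s: 4 to 12 weeks after surgery (abstract, Methods).
- Six cycles of 4 weeks, with floxuridine in the first 2 weeks of each (drug treatment plan).
- Conversion: 1 month = 365.25/12 days, so 3 months = 91.3 days = 13.04 weeks and 6 months = 182.6 days = 26.09 weeks.

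**Formulas** (weeks after surgery)
- End of cycle 6 = s + 6 × 4 = s + 24.
- End of the last floxuridine infusion = s + 5 × 4 + 2 = s + 22.
- HAIP received at 3 months = 13.04 − s.
- Time from the 6-month score to the end of cycle 6 = s + 24 − 26.09.
- Infusion k is complete by the 6-month score if s + 4(k − 1) + 2 ≤ 26.09.

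**Results**

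| | s = 4 | s = 8 | s = 12 |
|---|---|---|---|
| Weeks from 2-week score to first floxuridine | 2 | 6 | 10 |
| Weeks of HAIP at 3-month score | 9.0 | 5.0 | 1.0 |
| Infusions completed at 6-month score | 6 of 6 | 5 of 6 | 4 of 6 |
| End of last infusion (week) | 26 | 30 | 34 |
| End of cycle 6 (week) | 28 | 32 | 36 |
| Weeks from 6-month score to end of cycle 6 | 1.9 | 5.9 | 9.9 |

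With a start at exactly week 4, the last infusion ends on day 182 and the 6-month score falls on day 182.6, which is in effect a tie. With any start more than about half a day later, floxuridine is still running or still due after the last score.

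**Would later visits cover treatment?** Nine months = 273.9 days = 39.1 weeks, and 12 months = 52.2 weeks. The latest scheduled end of cycle 6 is week 36, so a 9-month score falls 39.1 − 36 = 3.1 weeks or more after it, and a 12-month score 52.2 − 36 = 16.2 weeks or more after it.

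**The case against.** The strongest reply is that this is one instrument among several. Blood counts and liver tests every 2 weeks follow the treatment calendar and cover the late cycles. Serious and grade 3 or higher events are recorded separately, and nothing ties them to the three scoring visits. How long they are collected is not stated, but a condensed article commonly leaves that to the full protocol. This stands. A reader might infer that late toxicity is missed altogether, or that arm B toxicity will necessarily be understated; the document supports neither. What remains is narrower. The laboratory tests are described only during HAIP and give no comparison with arm A. The interim reviews are triggered by inclusions and aim at early detection of high rates. Neither replaces a score after treatment.

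The size can also be overstated. Dividing the remaining cycle time by 24 weeks gives 1.9/24 = 8% to 9.9/24 = 41% unscored, but this counts the saline weeks. By infusions the range is 0 of 6 to 2 of 6, or 0% to 33%.

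The 2-week reading is not in itself a mistake, since it can serve as a baseline after surgery and before the drug. Nor does the article say that recording of pump complications stops at 3 months; it gives times only for the surgical complication score.

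Finally, the Follow-up section specifies both arms for quality of life but does not repeat this for the toxicity score. A scored comparison between arms is an inference from the stated objective of comparing adverse events.

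**Conclusion.** The point holds as a mismatch between two schedules that the article itself fixes. It is not a detail lost in condensation. One of the three scores precedes all floxuridine, the second reflects 1 to 9 weeks of HAIP depending on start date, and the third comes 1.9 to 9.9 weeks before the end of cycle 6, with 0 to 2 of the 6 infusions not yet complete. None follows treatment. The scored safety results can therefore understate late-cycle and post-treatment toxicity, mainly of lower grade.

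This rests on patients being on schedule; early stopping or held doses would change individual calendars. The article does not say whether a score looks back over the preceding interval. If it does, toxicity up to week 26.1 is covered, but still nothing after it.

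Severity: should be fixed. It affects a secondary safety endpoint and has no bearing on the primary endpoint or the sample size.

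**What to change.** Keep the 2-week reading and label it a pre-drug baseline. Keep the 3- and 6-month scores, and add scores at 9 and 12 months in both arms. State that each score covers the interval since the previous one. Both arms are then compared over a single window of 12 months from surgery that contains all scheduled HAIP and a post-treatment period.

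If per-cycle scores are also wanted in arm B, keep them out of the between-arm comparison: scoring one arm more often would raise its recorded event rate through ascertainment alone.

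The visits already exist, since CT and CEA are scheduled every 3 months in years 1 to 3 and quality of life every 3 months in the first year, in both arms. The cost is a change to the visit schedule and case report form, and a few more scoring forms per patient.
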